## Abstract

Endovascular interventions (EVI) are increasingly performed as minimally-invasive alternatives to surgery and have many advantages, including a decreased need for general anesthesia. However, EVI can be stressful for patients and often lead to anxiety and pain related to the procedure. The use of local anesthetics, anxiolytics, and analgesic drugs can help avoid general anesthesia. Nevertheless, these drugs have potential side effects. Alternative nonpharmacological therapies can improve patients’ experience during conscious interventions and reduce the need for additional medications. The added value of virtually augmented self-hypnosis (VA-HYPO) and its potential to reduce pain and anxiety during peripheral and visceral arterial and venous EVI is unknown. This is a prospective two-arm trial designed to randomize 100 patients in two groups according to the use or not of VA-HYPO during peripheral EVI as a complementary nonpharmacological technique to improve patient comfort. The main objective is to compare per-procedural anxiety, and the secondary aim is to compare the rated per-procedural pain in both groups. The potential significance is that VA-HYPO may improve patients’ experience during peripheral and visceral arterial and venous EVI and other minimally invasive interventions performed under local anesthesia.

**Trial registration**: Our study is registered on clinicaltrials.gov, with trial registration number: NCT04561596.

## Introduction

Endovascular interventions (EVI) are minimally invasive therapies gaining interest in many indications. EVI are increasingly replacing surgery and vastly reduce the need for general anesthesia. Indications for percutaneous interventions are many and varied; typical examples include treatments for venous disorders [1], aneurysms [2], and peripheral and visceral arterial diseases [3]. Interventions whose sole purpose is to gain vascular access, such as for peripherally inserted central catheters, are performed exclusively under local anesthesia [4]. Furthermore, outpatient procedures have been developed and expanded during the last decade [5]. Despite efforts regarding patient information, preparation, and management for EVI, patients often experience periprocedural apprehension, generating anxiety. During peripheral EVI–procedures primarily performed under local anesthesia–pain feelings at various levels are observed. Such states are not specific to EVI and have frequently been reported in patients admitted for cardiovascular surgery, ranging from 20% to 60% [6, 7]. Nonetheless, they might be exacerbated by the environment required for EVI, which includes complex facilities (X-ray and hybrid interventional suites), advanced devices and technologies. Associated uncontrolled overcommunication on social media and free websites by non-healthcare professionals, whose quality is variable, might induce ambiguity and inconsistency, leading to anxiety [8]. Furthermore, preoperative anxiety significantly influences postoperative pain and patient outcomes [9, 10], particularly because anxiety and pain interact synergistically.

Periprocedural anxiety and pain are most commonly managed with rapid-acting opioid analgesics and/or hypnotic sedative drugs [11–14]. With minimal (Level 1 of the American Society of Anesthesiology [15]) and moderate sedation/analgesia (Level 2), spontaneous ventilation and cardiovascular function are usually maintained. In contrast, more profound sedation (Level 3) might require intervention for adequate ventilation. Despite appropriate delivery of drugs and careful monitoring, complications may occur. Complications include respiratory depression, hypotension, unconsciousness, paradoxical agitation, and nausea or vomiting. Preprocedural anxiety might be treated with anxiolytics. However, some drugs (e.g., Lorazepam) failed to decrease preoperative anxiety significantly [11].

Nonpharmacological pain and anxiety management approaches have been developed as adjunctive treatment [16–18]. Hypnosis induces a state of reduced peripheral awareness and can be used as a nonpharmacological intervention to optimize patients’ experience during EVI procedures, with significant analgesic and anxiolytic effects [19–23]. Dissociation is the main effect of hypnosis used during conscious medical interventions. One of the main limitations of using hypnosis is the human resources required, limiting the number of patients who can benefit from it. Virtually augmented self-hypnosis is a technique that combines the immersive and inductive effect of virtual reality, followed by suggestions for comfort and pain relief [24].

In experimental and clinical experience, virtual reality is considered a valuable tool to decrease anxiety and reduce pain by diverting attention from painful stimuli [25, 26]. It is interesting to notice that the effect on pain has been observed in both highly hypnotizable and less hypnotizable patients [27, 28]. However, available data regarding the advantages of using virtually augmented self-hypnosis (VA-HYPO) in clinical practice remains scarce, and its impact on pain and anxiety related to EVI is unknown.

## Materials and methods

### ● Aim, design, and setting of the study

This prospective study is based in a single Swiss academic hospital and seeks to evaluate whether virtually augmented self-hypnosis (VA-HYPO) lowers anxiety and pain in the setting of percutaneous peripheral and visceral arterial and venous EVI. VA-HYPO is performed using a head-mounted device (Oncomfort^TM^) providing a video screen and sound system aiming to achieve digital sedation. For this study, patients follow the "Aqua" module reproducing a scuba diving experience and breath exercises in a virtual reality environment. For this purpose, a monocentric open-label prospective randomized trial with two arms is designed.

### ● Sample size, inclusion, and exclusion criteria

A power analysis was conducted to determine a sample size that can detect a statistically significant anxiety decrease of at least 5 percent, such as encountered in a previous investigation using autohypnosis in the setting of systemic chemotherapy [29]. The Sample size calculation is based on the primary outcome "per procedural anxiety". The expected mean (sd) of per procedural anxiety in the control group is 45 (3) and 5% lower in the intervention group 42.75 (2). The minimum sample size needed to show that the mean difference is significant with a power of 90% and an alpha of 5% (two-sided) is 32 patients per group. To avoid loss of power due to possible dropout (20%), randomizing 40 patients in each group would be appropriate. Furthermore, because the primary outcome measure is patient-reported and subject to measurement error, we intend to add a safety margin and include 50 participants in each group since no additional risk nor financial burden is associated with study participation.

Inclusion criteria: participants will be patients subjected to interventional radiology for a peripheral vascular intervention under local anesthesia; participants will be over 18 years old and have signed an informed consent form. In this study, peripheral EVI refers to lower limb arterial angioplasty and stenting, renal and mesenteric angioplasty and stenting, venous interventions (vena cava filter placement, venous malformation embolization, peripherally inserted central catheter). Patients referred to cardiothoracic or neuroradiology intervention are not eligible.

Exclusion criteria: no or limited study language comprehension, deafness or visually impaired patient, the anticipated need for a sedative medication, a history of motion sickness or a psychiatric disease such as paranoia, schizophrenia, deep water phobia, and dementia. We will also exclude patients who do not tolerate the virtual reality mask during a preoperative visit.

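### The stated minimum of 32 patients per group does not follow from the stated inputs, which give 28 with the planned t-test; a minor, conservative error

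*Protocol article*

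**What the plan says.** The protocol article, section *Sample size, inclusion, and exclusion criteria*, sizes the trial on the primary outcome, per-procedural anxiety. Its assumptions are: "The expected mean (sd) of per procedural anxiety in the control group is 45 (3) and 5% lower in the intervention group 42.75 (2"), with the number in brackets being the SD. It calls the resulting figure the minimum needed for the mean difference to be "significant with a power of 90% and an alpha of 5% (two-sided) is 32 patients per group". It then raises this to 40 per group for 20% dropout, and to 50 per group as a declared safety margin because the outcome is patient-reported and subject to measurement error.

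The section *Characteristics of participants, randomization, and blinding* gives 1:1 allocation. The section *Type of data and statistical analyses* says that the means of the anxiety score will be compared with two-sided Student tests. The 90% power is attached to the 32; no power is stated for 40 or 50.

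**The concern.** Everything a two-group comparison of means needs is printed: both means, both SDs, alpha, sidedness, power, allocation and test. The result should therefore be reproducible to within a patient or so, whichever standard formula was used. It is not.

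What is at stake is limited. The paragraph is the plan's evidence that the trial is adequately sized, and the section *Limitations of the study design* relies on the power analysis when it expects robust results. A figure presented as a minimum that is not the minimum leaves the reader unsure whether the printed inputs are the ones that were used.

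**Working it through.** **Inputs** (from *Sample size, inclusion, and exclusion criteria*, except allocation and test, whose sections are named above)

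- Difference: 45 − 42.75 = 2.25, which is 5% of 45, as stated.
- SDs: 3 and 2, so the sum of variances is 9 + 4 = 13, the pooled SD is √(13/2) = 2.55, and the standardised difference is 2.25/2.55 = 0.88.
- Alpha 5% two-sided, power 90%, allocation 1:1, Student t-test.

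**Step 1. Normal approximation.** n per group = (z₀.₉₇₅ + z₀.₉₀)² × (SD₁² + SD₂²) / difference² = (1.960 + 1.2816)² × 13 / 2.25² = 26.98, so 27.

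**Step 2. t-test.** Power comes from the noncentral t distribution with noncentrality 2.25 / √(13/n). With equal groups the Student and Welch statistics have the same standard error and differ only in degrees of freedom.

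| n per group | Student t | Welch |
|---|---|---|
| 27 | 88.9% | 88.7% |
| 28 | 90.0% | 89.9% |
| 29 | 91.0% | 90.9% |
| 32 | 93.5% | 93.4% |
| 40 | 97.4% | 97.3% |
| 50 | 99.2% | 99.2% |

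The minimum for 90% is 28 with the Student test and 29 with Welch. The stated 32 is 4 above 28, and 4/28 = 14%. That exceeds the spread between the three methods (27 to 29).

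**Step 3. Is 32 a simple slip in one setting?** On the t-test, changing one input at a time gives:

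- one-sided test: 23
- 80% power: 22
- 95% power: 35
- alpha 2.5%: 34
- SD 2.5 in both groups: 27
- SD 3 in both groups: 39

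None of these is 32. Power of 80% together with alpha 1% does give 32, but that needs two stated inputs to be wrong at once.

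**Step 4. The later steps.** 32 / (1 − 0.20) = 40, so the dropout adjustment is done correctly on its starting figure. From 28 it would be 28 / 0.80 = 35 (from 29, 36.25, so 37). Of the planned 50, 20% dropout leaves 50 × 0.80 = 40 evaluable. On the stated SDs that gives 97.4% power, and 99.2% if nobody is lost.

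**The case against.** The strongest reply is that nothing turns on this. On the printed inputs 32 is more than enough, the plan goes on to 50, and no test, estimate or decision depends on 32 rather than 28. That is right, and it is why the point is minor. It does not make 32 the minimum that the paragraph says it is.

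A second reply is that an allowance for a rank test may lie behind the figure. Inflating the normal value by 15% gives 26.98 × 1.15 = 31.03, which rounds up to 32. A simulated Mann-Whitney test with normal data on the stated means and SDs needs about 31 (89.8% power at 30, 91.1% at 31). This is plausible and would be harmless. But the article mentions no such allowance. It speaks of a difference in means and names Student tests for the anxiety score; the only rank test it names is for the qualitative data.

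A third reply is that an article leaves formula and software to the full protocol. That is fair for a detail left out, but here a full set of inputs is printed beside a result that does not follow from them.

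Three stronger readings are tempting, and the article does not support them:

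- *That the plan claims 90% power for 50 per group.* It attaches 90% to 32 only and declares the 50 as a margin. Recruitment was still open, so 50 is a planned number.
- *That the 50 is wrong because it is derived from the 32.* Only the 40 is computed from 32. The 50 is a judgement with no formula, and starting from 28 would not change it.
- *That alpha was split, or a common SD of 3 was used, so that the real power at 32 is lower.* The article states alpha 5%, one primary outcome and two different SDs. On the t-test, alpha 2.5% needs 34 rather than 32. Such explanations contradict the printed inputs.

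**Conclusion.** Wrong as written, and minor. On the stated means, SDs, alpha and power, and with the test the plan names, the minimum is 28 per group, not 32. At 32 the power is about 93.5%. The discrepancy is conservative: the trial is not underpowered on its stated assumptions, and the planned 50 per group more than meets the 90% target.

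The conclusion rests on the printed inputs being the ones intended. The powers quoted for 40 and 50 depend wholly on the SDs of 3 and 2; they describe the plan's own assumptions and do not predict what the trial will achieve.

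**What to change.** Correct the one paragraph in *Sample size, inclusion, and exclusion criteria* in one of two ways.

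1. Give the minimum as 28 per group (two-sided Student t-test, SDs 3 and 2) and 35 after 20% dropout. Keep the 50 as the declared margin, and add that on these SDs it gives about 97% power with 40 evaluable and 99% with all 50.
2. If 32 came from another input or test, state that input or test, and make it agree with the Student test in *Type of data and statistical analyses*.

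The cost is a wording change. The number enrolled, the conduct of the trial and the primary comparison stay as they are, unless the second route shows that a different test was intended.

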### ● Characteristics of participants, randomization, and blinding

The sequentially numbered, opaque, sealed envelope (SNOSE) method was used for randomization with a 1:1 allocation before the intervention. A person not involved with patient recruiting will print the allocation sequence and prepare the envelopes ([name]).

One group of participants will wear the virtual reality mask with the autohypnosis program running during the EVI. The other group will benefit from the intervention in standard conditions without the virtual reality mask.

The study will run in an open-label fashion because information cannot be withheld from trial participants and operators. Participants included in the virtual reality arm will wear the head-mounted device, and awareness regarding self-hypnosis is inevitable.

Study timetable: the first patient was included in August, 2020. The recruitment is expected to be completed by the end of May, 2022.

All vascular punctures are performed under local anesthesia and using ultrasound guidance. The puncture site depends on the clinical indication and is at the operator’s discretion. The typical vascular access is the common femoral artery for peripheral and visceral arterial interventions. The most common venous accesses are the common femoral vein and brachial veins.

Arterial vascular accesses usually benefit from vascular closer devices, at the operator’s discretion, while venous accesses are controlled by manual compression.

### ● Processes, interventions, and comparisons

The schedule of enrolment, interventions, and assessment is presented in Fig 1. On the day of the intervention, after randomization, the participants will fill the operative anxiety self-questionnaire (Table 1) and indicate the intensity of pain felt on a segmented numerical version of the analog visual scale (Table 2). At the patient’s arrival in the operating room, an investigator will adapt the virtual reality mask if the patient is in the virtual reality group.

**Fig 1 pone.0263002.g001:**
[figure not shown]
Schedule of enrolment, interventions, and assessments.

**Table 1 pone.0263002.t001:** Anxiety scale used before and after the endovascular intervention.

		Not at all	A little	Somewhat	Very much so
**1.**	I feel calm	**1**	**2**	**3**	**4**
**2.**	I feel secure	**1**	**2**	**3**	**4**
**3.**	I feel tense	**1**	**2**	**3**	**4**
**4.**	I feel strained	**1**	**2**	**3**	**4**
**5**	I feel at ease	**1**	**2**	**3**	**4**
**6.**	I feel upset	**1**	**2**	**3**	**4**
**7.**	I am worrying about possible misfortunes	**1**	**2**	**3**	**4**
**8.**	I feel satisfied	**1**	**2**	**3**	**4**
**9.**	I feel frightened	**1**	**2**	**3**	**4**
**10.**	I feel comfortable	**1**	**2**	**3**	**4**
**11.**	I feel self-confident	**1**	**2**	**3**	**4**
**12.**	I feel nervous	**1**	**2**	**3**	**4**
**13.**	I feel jittery	**1**	**2**	**3**	**4**
**14.**	I feel indecisive	**1**	**2**	**3**	**4**
**15.**	I am relaxed	**1**	**2**	**3**	**4**
**16.**	I feel content	**1**	**2**	**3**	**4**
**17.**	I am worried	**1**	**2**	**3**	**4**
**18.**	I feel confident	**1**	**2**	**3**	**4**
**19.**	I feel steady	**1**	**2**	**3**	**4**
**20.**	I feel pleasant	**1**	**2**	**3**	**4**

This questionnaire will be presented to participants in the French language, according to Gauthier et al. [30].

**Table 2 pone.0263002.t002:** Pain assessment scale used before and after the endovascular intervention.

Absence of pain	**1**	**2**	**3**	**4**	**5**	**6**	**7**	**8**	**9**	**10**	Worst pain imaginable

Participants will be asked to indicate the pain they currently feel on the pain scale (0 = absence of pain; 10 = worst pain imaginable).

The percutaneous EVI is performed as usual except for the autohypnosis software that will run during the intervention in the virtual reality group.

The medical team will provide pain and anxiolytic medication if needed during the intervention at the operator’s discretion and depending on the patient’s condition.

Immediately after the intervention, participants will fill a second self-questionnaire (postoperative questionnaire) to report anxiety and pain felt during the intervention (Tables 1 and 2).

A clinical visit at 3 months, as part of the standard clinical protocol, is planned for late assessment. Participants will fill a third self-questionnaire on anxiety (Table 1), the visual analog scale for pain (Table 2), and remembered per-procedural impressions (Table 3).

**Table 3 pone.0263002.t003:** Post-procedural remembered impressions.

Pleasant	**1**	**2**	**3**	**4**	**5**	**6**	**7**	**8**	**9**	**10**	Uncomfortable

At the 3-month visit, participants will be asked to indicate their current feelings related to the intervention on the following scale (0 = pleasant; 10 = uncomfortable)

If needed, would you be ready to repeat the experience?

Yes / Maybe / No.

The study flowchart from referral to the last clinical visit is provided in Fig 2.

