## ● Measured outcomes

The primary outcome is the rated per procedural anxiety, measured by the Spielberger Anxiety State Inventory in French [30]. The Spielberger Anxiety State Inventory is a self-questionnaire of 20 items, each item scores from 1 to 4. The test result is the sum of the 20 items; therefore, the results range from 20 to 80 (Table 1). A high score is related to a high level of anxiety at the moment of the test.

The secondary outcome is the rated per procedural pain measured by the visual analog pain scale. The visual analog pain scale rates pain from 0 to 10, 0 being no pain, and 10 being the worst pain imaginable (Table 2).

Both outcomes will be measured on day 1, before and after the intervention, and 3 months after the intervention.

The other outcomes of interest will be measured on day 1. Those outcomes are age and sex, side effects of virtual reality, the amount of drugs administered for pain and anxiety, the number of participants that did not tolerate the mask before randomization, and the number of participants where the mask has been taken off (patient decision/medical team decision). We will measure the prevalence of cybersickness, our safety outcome on day 1.

Patient-relevant outcomes, including amputation, mesenteric or renal ischemia, and death, will be reported 90 days after EVI.

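### The protocol contradicts itself on the recall period of its primary and secondary outcomes: the time of the procedure, or the moment the form is filled in

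*Protocol article*

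**What the plan says.** All references are to the protocol article.

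**Target of measurement.** Measured outcomes names per-procedural anxiety as the primary outcome and adds: "The secondary outcome is the rated per procedural pain measured by the visual analog pain scale". In Processes, interventions, and comparisons, the text after Table 2 says that, directly after the procedure, "participants will fill a second self-questionnaire (postoperative questionnaire) to report anxiety and pain felt during the intervention", and it refers to Tables 1 and 2 as the forms.

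**Pain form.** The caption of Table 2 reads "Pain assessment scale used before and after the endovascular intervention". The only instruction printed beneath it is: "Participants will be asked to indicate the pain they currently feel on the pain scale".

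**Anxiety form.** The caption of Table 1 reads "Anxiety scale used before and after the endovascular intervention". All 20 items are in the present tense, for example "I am worrying about possible misfortunes". Measured outcomes says of the score: "A high score is related to a high level of anxiety at the moment of the test".

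**Timing.** Both outcomes are assessed before the procedure, after it, and at 3 months, with Tables 1 and 2 named again for the 3-month visit. No assessment during the procedure is described.

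**The concern.** The trial asks whether virtually augmented self-hypnosis lowers distress while the endovascular procedure is under way. The post-procedure form is completed when the procedure has ended and the program is no longer running. A patient who follows the printed wording then reports the state at that later moment.

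If that happens, a null result could mean only that both arms had settled by then, and a positive result would not by itself show benefit during the procedure. No later analysis can recover a recall period that patients were not asked about. This is therefore a matter for the protocol and its forms. It is also a conflict between stated texts, so it cannot be put down to detail left for another document.

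**Working it through.** **1. The texts side by side**

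| Outcome | Stated target | Wording of the form | Reference time stated for the score | Conflict |
|---|---|---|---|---|
| Pain (secondary) | During the procedure | Instruction asks for present pain | None beyond that instruction | Explicit |
| Anxiety (primary) | During the procedure | Present-tense items; no header shown | Time of completion | Implied |

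The sentence on the postoperative questionnaire states an intention and then refers to these same two tables. No version worded for recall of the procedure is described. One printed wording is thus asked to serve three occasions, and at 3 months a present-moment instruction cannot refer to the procedure.

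**2. The plan's own sample size**

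Inputs from the sample size section: means 45 and 42.75, SDs 3 and 2, power 90%, two-sided alpha 5%, stated minimum 32 per group, dropout 20%, final 50 per group. The statistical analyses section names two-sided Student tests.

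- Difference: 45 − 42.75 = 2.25.
- Root-mean-square SD: √((3² + 2²)/2) = √6.5 = 2.55.
- Normal approximation: n = 2 × (1.960 + 1.282)² × 6.5 / 2.25² = 27 per group.
- Exact t: 28 per group. Welch: 29.
- Power of the t test at 32 per group: 93.5%.
- Dropout: 32/(1 − 0.20) = 40, as stated.

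The figure of 32 is not reproduced, but it errs on the large side. That is a separate matter and does not bear on this point.

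**3. What dilution could cost for anxiety (illustration)**

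Let f be the share of the 2.25-point difference that remains when the form is answered for the moment just after the procedure. Hold the SDs fixed. For the two-sample t test with n per arm:

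- noncentrality = 2.25 f / (2.55 × √(2/n)), with 2n − 2 degrees of freedom;
- power = probability that the noncentral t exceeds the two-sided 5% critical value in absolute size.

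At n = 50 the denominator is 2.55 × 0.2 = 0.510, so f = 1 gives a noncentrality of 2.25/0.510 = 4.41. At n = 40 (50 less 20% dropout) it is 2.55 × 0.2236 = 0.570, giving 3.95.

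| f | Difference | Power, 50 per arm | Power, 40 per arm |
|---|---|---|---|
| 100% | 2.25 | 99% | 97% |
| 75% | 1.69 | 91% | 83% |
| 50% | 1.125 | 59% | 50% |
| 25% | 0.56 | 19% | 16% |

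The document gives nothing from which to estimate f. It also gives no expected means or SDs for pain, so no matching calculation is possible for the outcome where the conflict is explicit.

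**The case against.** The strongest case on the other side is that the one sentence specific to the post-procedure administration says what it is for: what was felt during the intervention. The table captions say the scales are used before and after. They do not say that headers or instructions are identical on each occasion. The anxiety form is presented in a cited French version whose instruction is not shown, and a condensed article need not print it. The statement that the score reflects the moment of the test may be a general description of the instrument.

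Much of this stands, and it limits what can be claimed:

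- A reader might infer that the postoperative questionnaire does measure how patients feel once the procedure is over. The document does not establish that. It supports only that the texts disagree, and that forms followed as printed would have this effect.
- A reader might infer that patients receive spoken corrections, and that in an open-label trial these differ by arm. Nothing in the document describes such prompting.
- A reader might take one row of the power table, such as 59%, as the expected loss. Each row is an assumption. With 75% of the difference retained, power at 50 per arm is 91%, still above the planned 90%.
- The two outcomes should not be given equal weight. The anxiety conflict rests on item tense and the general description of the score, and the pain conflict rests on a printed instruction.

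What does not stand is the view that this is only omitted detail. The article prints a recall period for pain that contradicts its own outcome definition.

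**Conclusion.** The concern holds as an internal contradiction on the recall period of both outcomes, explicit for pain and implied for anxiety. Which wording patients actually receive cannot be told from the document.

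If the forms are used as printed, the trial records the immediate post-procedural state, and the contrast between arms may be diluted. Across the assumed range of retained difference, from 100% down to 25%, power for anxiety at 50 per arm runs from 99% to 19%. This rests on the plan's own means and SDs, unchanged SDs after the procedure, and a retained share that is unknown. Because the meaning of the primary outcome is affected, the passages need to be reconciled before the results are interpreted.

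**What to change.** 1. On the post-procedure administration of Tables 1 and 2 only, add a header instruction. For anxiety: *Answer for how you felt during the procedure.* For pain: *Rate the pain you felt during the procedure.*
2. Leave the 20 items of the cited French version as they are. Rewording them would depart from the instrument the protocol commits to.
3. Keep the current-state wording on the pre-procedure and 3-month forms.
4. Align the note under Table 2 and the description of the anxiety score in Measured outcomes with these instructions.
5. If the forms in use already carry such an instruction, correcting those two passages is enough.
6. If they do not, record which instruction each enrolled patient received, report a sensitivity analysis by form version, and describe results obtained under the present-moment wording as immediate post-procedural state.

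**Cost.** A one-line header on each of two forms, an ethics notification, and a form-version field in the database. The real downside is two instruction versions within one trial. Recruitment began in August 2020 and was expected to finish by the end of May 2022, so the share of patients under each version depends on when the change is made. Redefining both outcomes as post-procedural state would also reconcile the text, but it would give up the stated aim.
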